### Data collection

Data on primary and secondary outcomes will be collected at baseline, post-intervention (after 18 weeks), and three months after post-intervention. All questionnaire data will be coded and collected using an Internet-administered data collection tool stored and secured on servers at Uppsala University.

Participants will be contacted by telephone by a research nurse if they do not complete the baseline assessment within 1 week, to resolve any potential hindrances to completing the questionnaires; they will subsequently receive reminders via SMS and e-mail if they do not complete the assessment within 1 week, and again after 1 week if it is still not completed. At the assessments post-intervention and three months later, participants will be informed about the assessments one week ahead, via SMS and e-mail, and then be reminded via SMS and e-mail if they do not respond within 1 week after being asked to do so, and again, if still not responding, after 1 more week.

#### Medical and socio–economic background data

Data regarding the patients’ HNC and cancer treatment will be collected from regional healthcare registers, based on clinical data. ICs’ socioeconomic background will be self-reported at baseline, using project-specific questions concerning civil status, parental status, relation to the patient, education level, work situation, economic status, computer skills, and Swedish-language ability.

#### Primary outcome

The Preparedness for Caregiving Scale [34] measures ICs’ perceived preparedness to provide care. It consists of eight items, responded to using 5-point Likert scales ranging from 0 = “not at all prepared” to 4 = “very well prepared.” The items concern the preparedness to: care for the patient, including emergencies (5 items); to find out about and set up services (1 item); to get support from the healthcare system (1 item); and to manage the stress related to being an IC (1 item). The scores are summed to a scale of 0–32, with a higher score reflecting better preparedness. It has been judged to be valid, reliable, and user friendly according to a psychometric evaluation in a Swedish sample of ICs [35].

#### Secondary outcomes

The Caregiver Burden Scale (CBS) [36, 37] comprises 22 items responded to on a 4-point Likert scale ranging from 1 = “not at all” to 4 = “often,” with a higher score indicating more burden. The 22 items can be organized into the following factors, i.e., general strain, disappointment, emotional involvement, environment, and isolation, and the mean of all items indicates the total burden. The CBS is designed to be valid regardless of the patient’s diagnosis and has been used to measure burden among Swedish ICs to patients with various diagnoses.

The RAND-36 [38] is a widely used health-related quality of life questionnaire with good psychometric properties. It measures physical functioning, role limitations due to physical and emotional health problems, social functioning, emotional well-being, energy/fatigue, pain, and general health perceptions. Physical and mental health summary scores may also be calculated. Current Swedish reference values are available [39].

The Depression Anxiety Stress Scale-21 (DASS-21) [40, 41] comprises three 7-item subscales measuring depression, anxiety, and stress. Each item is scored on a 4-point Likert scale, with higher scores indicating more symptoms. The DASS-21 has good psychometric properties, is deemed feasible for research and clinical practice, and has been used in samples of ICs [42].

#### ICs’ use of Carer eSupport: logged data

The ICs’ activity in Carer eSupport will be logged automatically. Logged data will concern the dates and times of log-ins, duration of logged-in periods, use of (i.e., clicks on) text, lectures, and videos, reading of and participation in discussion forums, and reading of and posed questions in the Q&A section.

#### ICs’ satisfaction with Carer eSupport

A subsample of ICs (*n* = 20) of various genders and ages who have had access to Carer eSupport will be asked to participate in a semi-structured individual interview within 1 month post-intervention. The interview will cover their experiences of the relevance, acceptability, and usability of Carer eSupport. In addition, all ICs randomized to Carer eSupport plus SAU will be asked to complete a project-specific questionnaire at the post-intervention follow-up regarding their satisfaction with and perceived benefits of Carer eSupport.

#### Additional professional support and internet use

ICs randomized to SAU only will be asked whether they have received support from professionals (no, occasionally, regularly) and/or whether they have used the Internet for support during the patient’s disease and treatment, using project-specific questions. ICs randomized to Carer eSupport plus SAU will be asked whether they have received support from professionals and/or via the Internet in addition to Carer eSupport. The questions will be administered post-intervention and 3 months post-intervention.

### Data processing and analysis

The effect of Carer eSupport plus SAU on preparedness for caregiving and secondary outcomes, compared with SAU, will be evaluated by intention to treat (ITT) analyses. Linear regression models, mixed-model regression, or ANCOVA will be used. All models will be adjusted for baseline measures, gender, and age. The multiple imputation technique will be used to impute the missing data if they can be assumed to be missing at random. Cohen’s *d* will be calculated to measure the effect size. Sensitivity analyses of the impact of noncompliance will include complete cases and per-protocol analyses. Logged data regarding ICs’ use of Carer eSupport will be analyzed using descriptive statistics. According to Braun and Clarke, the individual interviews will be transcribed verbatim and analyzed using thematic analysis [43].

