We used the theoretical framework, the results of focus group discussions (presented in “Background”), and existing scientific evidence to develop the first version of Carer eSupport in collaboration with healthcare professionals and an expert group including the ICs of patients with HNC. Thirty-two ICs of patients with HNC have tested that first version in a feasibility study conducted in 2023. The ICs had access to Carer eSupport for one month, after which they completed the questionnaires that will be used in the RCT (described below). Nineteen of 32 ICs took part in individual interviews after 1–2 months regarding their experience of Carer eSupport and their opinions about how it could be improved. Data from the feasibility study were analyzed according to our predefined feasibility criteria [24], i.e., ≥ 45% gave written consent, ≥ 50% used Carer eSupport, < 30% discontinued participation, ≥ 50% completed the questionnaires, and whether Carer eSupport was considered acceptable, relevant, and usable according to the interviews. The analysis revealed that 32 of 52 approached ICs (62%) gave written consent, 22 of them (69%) used Carer eSupport, according to logged “clicks” on text and video files, 16 (50%) completed the questionnaires, and nine (28%) discontinued participation. The ICs experienced Carer eSupport as relevant, helpful, and usable, according to the interviews. However, they gave suggestions for improving Carer eSupport, for example, adding content and improving website design, which have been implemented accordingly. In addition, important knowledge of the recruitment and data collection procedures was obtained. One important finding was the ICs’ experience that the data collection included too many questions. That led to the decision to exclude a fatigue scale since fatigue is the least significant outcome measure compared with our remaining outcome measures, according to previous research [11, 13]. The conclusion was that Carer eSupport and the associated research procedures are feasible after the improvements and can be employed in the RCT. The feasibility study will be reported in detail elsewhere.

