### Support as usual (SAU)

SAU comprises the possibility of ICs contacting a specified nurse with expertise in HNC, at the ENT or oncology clinic, to ask for support. These contacts are commonly restricted to occasional appointments and/or phone calls. Healthcare counselors at the clinics are also available for ICs on request. Also, the Swedish healthcare system is always responsible for recognizing the need to support the children (< 18 years old) of patients with cancer; nurses, physicians, and healthcare counselors commonly coordinate that support within Swedish cancer care. Support groups providing emotional and social support to the ICs of patients with various cancer diagnoses may also be arranged on occasion at the clinics. However, Internet-administered support, tailored to the needs of ICs of patients with HNC, is not available in SAU.

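### The two sensitivity analyses named for noncompliance do not answer that question: complete-case analysis addresses missing data, and per-protocol selection on use falls on one arm and gives up the randomized comparison

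*Protocol article*

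**What the plan says.** Under Data processing and analysis, the protocol article states that the effect of Carer eSupport plus SAU, "compared with SAU, will be evaluated by intention to treat (ITT) analyses". On covariates it says "All models will be adjusted for baseline measures, gender, and age", and on missing data "The multiple imputation technique will be used to impute the missing data if they can be assumed to be missing at random". It then turns to noncompliance: "Sensitivity analyses of the impact of noncompliance will include complete cases and per-protocol analyses". The wording leaves the list open, but no complier effect or other randomization-based estimate is named. On usage it says "Logged data regarding ICs’ use of Carer eSupport will be analyzed using descriptive statistics".

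Three other sections bear on the point:

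- **Support as usual (SAU):** "However, Internet-administered support, tailored to the needs of ICs of patients with HNC, is not available in SAU".
- **ICs' use of Carer eSupport: logged data:** log-ins and clicks are recorded automatically within Carer eSupport, so use is measured only for ICs who have access.
- **Development and feasibility testing:** of 32 consenting ICs with one month's access, "22 of them (69%) used Carer eSupport" and 16 completed the questionnaires. The internal pilot lets the trial proceed if at least 50% use the support.

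**The concern.** The article names a question, the impact of noncompliance, and two tools for it.

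The first tool selects on response. An IC who never logs in but returns the questionnaires stays in a complete-case analysis, and a heavy user who does not respond drops out. The Discussion treats stopping use and loss to follow-up as two things; the analysis sentence merges them.

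The second tool, if the set is based on use of Carer eSupport, selects on behaviour after randomization that can be observed in one arm only. Users who remain are then compared with SAU ICs who include people who would not have used the support. Any difference between those two kinds of IC enters the estimate. The article itself points to strain and unfamiliarity with devices as barriers. Computer skills are recorded at baseline but are not in the stated adjustment set.

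At stake is interpretation. If the per-protocol estimate differs from intention to treat, it cannot be said whether use or selection is the reason.

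**Working it through.** **1. The plan's own figures.** Use in the feasibility study: 22/32 = 0.6875, the stated 69%; non-use 10/32 = 0.3125. The sample size also reproduces: a two-sided 5% test of one regression coefficient with f² = 0.15 has power 0.805 at N = 55, and 55/(1 − 0.5) = 110. Nothing below changes these.

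**2. Response is not use.** With 22 users and 16 questionnaire completers among the same 32 ICs, at least 22 − 16 = 6 users did not complete. A complete-case set there would have dropped at least six users and could have kept non-users.

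**3. Per-protocol bias.** Let π be the share who use the support when offered it, and g the user-minus-non-user outcome difference, in SD, absent any intervention effect and after covariate adjustment. If users are compared with all SAU ICs, the expected difference without any effect is

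μ(users) − [π μ(users) + (1 − π) μ(non-users)] = (1 − π) × g.

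The values of g are assumptions, since the documents give none.

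| π | Source | g = 0.3 SD | g = 0.5 SD |
|---|---|---|---|
| 0.6875 | feasibility study | 0.3125 × 0.3 = 0.09 | 0.3125 × 0.5 = 0.16 |
| 0.50 | pilot criterion | 0.5 × 0.3 = 0.15 | 0.5 × 0.5 = 0.25 |

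A negative g gives the same sizes with the opposite sign.

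**4. Simulation check.** Settings: 55 per arm, full follow-up, no covariates, no true effect, 5,000 trials per setting.

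| π | g (SD) | Mean per-protocol estimate | Rejection rate at nominal 5% |
|---|---|---|---|
| 0.6875 | 0.2 | 0.06 | 6% |
| 0.6875 | 0.5 | 0.16 | 12% |
| 0.6875 | 0.8 | 0.25 | 22% |
| 0.50 | 0.2 | 0.10 | 7% |
| 0.50 | 0.5 | 0.25 | 18% |
| 0.50 | 0.8 | 0.40 | 38% |

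In all settings run, intention to treat rejected in about 5% of trials and the complier estimate averaged within 0.02 SD of zero.

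**5. The complier effect.** With no access in SAU, and if allocation alone does nothing for non-users, the complier effect = ITT/π. An ITT effect of 0.40 SD (illustrative) at 69% use gives 0.40/0.6875 = 0.58 SD. The standard error scales alike: 1/0.6875 = 1.45 times that of ITT, or 1/0.50 = 2 times. Estimate and standard error are divided by the same number, so the test is in effect the ITT test.

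With a true complier effect of 0.5 SD, π = 0.6875 and g = 0.5 SD, the simulated means were ITT 0.34, per-protocol 0.66 and complier 0.49. The expected values are 0.6875 × 0.5 = 0.34, 0.5 + 0.16 = 0.66, and 0.50.

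**The case against.** The strongest case on the other side is that the stakes are low. Intention to treat is the main analysis, the criticised methods are labelled sensitivity analyses, the list is open, and reporting per-protocol beside intention to treat is conventional. The definition of the per-protocol set is properly left to the analysis plan, and its absence from an article is no finding. This stands and limits the severity, but the article does commit to complete-case analysis as a noncompliance analysis, and that is a mismatch on its face.

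Several stronger readings are tempting, and the documents do not support them:

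- **That both analyses set users against all SAU ICs.** Complete-case analysis does not, because it drops non-responders in both arms. Even for per-protocol, keeping every SAU IC is an inference: a set might also exclude for eligibility or timing. Only selection on use is necessarily one-armed.
- **That the bias favours the intervention.** Its sign is that of the gap. More strained or less prepared ICs might use the support more, which would reverse it. For complete cases, nothing in the article shows differential response by arm.
- **That the sizes shown are what the trial would see.** The gaps are assumed, and adjustment for baseline, gender and age removes whatever part of the gap those variables explain. The 69% comes from one month with a first version of the support, whereas the trial offers 18 weeks with an improved one. The calculation also ignores attrition, expected at up to 50%.
- **That a complier estimate is simply unbiased.** It needs the exclusion restriction, which is open to debate with self-reported outcomes. It does not solve missing outcomes, and it rescales intention to treat rather than adding evidence.

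**Conclusion.** The point holds and is minor. As named, complete-case analysis answers a missing-data question. A per-protocol analysis selected on Carer eSupport use gives up the randomized comparison. Neither estimates the effect of use from that comparison, although one-sided access and logged use make such an estimate possible.

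For residual gaps of 0.3 to 0.5 SD, the per-protocol bias is about 0.09 to 0.16 SD at 69% use and 0.15 to 0.25 SD at 50% use, in the direction of the gap. These figures rest on the assumed gaps, on exclusion for non-use alone, on retention of all SAU ICs and on full follow-up.

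A reader might infer that the trial's main conclusion is at risk. It is not: the primary test, sample size and alpha are untouched, and only the noncompliance analyses and their interpretation are affected.

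**What to change.** 1. Name a complier average causal effect as the main noncompliance analysis. Use two-stage least squares with randomized arm as the instrument and any logged use as the exposure, with the same covariates and imputed data as the primary model. Fix the definition of use before outcome data are seen; the click-based measure of the feasibility study is available.
2. State the exclusion restriction: allocation alone has no effect on ICs who do not use the support. A threshold above first use would strain it, because ICs below the threshold may still benefit. State also that logged clicks may miss use of downloaded material.
3. Report per-protocol results, if kept, as descriptive only.
4. Relabel complete-case analysis as a sensitivity analysis for missing data, beside multiple imputation.

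The cost is some wording and one extra model on data already collected. The statistical price is a standard error about 1.45 times that of intention to treat at 69% use and 2 times at 50%, with no power beyond intention to treat.

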## Discussion

This study protocol outlines an RCT investigating the effects of the Internet-administered Carer eSupport plus SAU on preparedness for caregiving, caregiver burden, and well-being in the ICs of patients with HNC, in comparison with those receiving SAU only. This discussion section synthesizes the protocol’s key points, contextualizes the study’s significance, discusses strengths and potential challenges, and outlines implications for clinical practice and future research.

The significance of this study lies in addressing unmet needs of ICs, who play a crucial role in the care of patients with HNC but often lack adequate support [11, 12]. Lack of preparedness and caregiver burden can harm the ICs and the quality of care they provide to the patients [1, 6, 13]. By evaluating the effectiveness of an Internet-administered support intervention tailored to the specific needs of the ICs of patients with HNC, this study seeks to reduce the gap between research and clinical care.

The strengths of this study include the careful design of Carer eSupport based on focus groups with the ICs of patients with HNC and healthcare professionals with expertise in HNC care [11, 24, 25], and the involvement of healthcare professionals and ICs in the development of the intervention. These features are pinpointed as essential for any possible future implementation of Carer eSupport in routine clinical care but are lacking in existing research regarding support directed to ICs [20]. Our multidisciplinary research group, including expertise in human–computer interaction, is unique and an additional strength, since usability is key to facilitating long-term engagement in Internet-administered support [21, 22]. The results of the feasibility study met the preset criteria for feasibility [24] and identified how Carer eSupport and the study procedures could be improved, thereby increasing the possibility for a productive RCT.

However, several challenges and considerations need to be acknowledged in implementing this study. First, recruiting and retaining participants, particularly ICs who may already be under significant stress, is challenging. High attrition rates are anticipated due to the strained situation of ICs and potential unfamiliarity with digital platforms. The phenomenon of participants who stop using the support or are lost to follow-up is a common challenge in trials evaluating Internet-administered support [44]. Efforts to mitigate these challenges, such as offering user-friendly interfaces and providing adequate support, are crucial. In addition, usage metrics such as logged data and determinants of attrition need to be analyzed, reported, and discussed to further our knowledge regarding this important topic.

If proven effective, Carer eSupport has the potential to significantly improve the well-being of ICs and enhance their preparedness for caregiving. Integrating Internet-administered support interventions into routine clinical care for patients with HNC and their ICs could lead to more comprehensive and holistic care approaches. Findings of this study may contribute to the development of tailored interventions for ICs of patients with other cancer types or chronic illnesses. Future research could explore the long-term effects of Carer eSupport, evaluate its cost-effectiveness, and investigate factors influencing its implementation and sustainability in real-world clinical settings.

In conclusion, this RCT protocol outlines an evaluation of the efficacy of Internet-administered support for the ICs of patients with HNC. By addressing the unmet needs of ICs, this study also has the potential to improve the quality of care provided to patients with HNC and enhance the well-being of not only their ICs but also the patients themselves.

## Data Availability

The researchers will have access to the final trial dataset in the presented RCT. The data will not be openly accessible at the participant level due to the General Data Protection Regulation (2016/679). However, de-identified data may be available for inclusion in systematic reviews and the like, on request.

## Abbreviations

ANCOVA: Analysis of covariance
Carer eSupport: The intervention
HNC: Head and neck cancer
IC: Informal caregiver
ITT: Intention to treat
RCT: Randomized controlled trial
SAU: Support as usual
SCT: Social cognitive theory
UTAUT: Unified theory of acceptance and use of technology
